#### **14.4 PROTECTION OF PRIVACY AND CONFIDENTIALITY**

##### **14.4.1 Privacy of individual**

Individual data such as positive RDT tests for malaria and anaemia will be reported to the participant at point of care, to relevant study staff, the antenatal care doctor where appropriate and will be recorded in the child's health passport in addition to study CRFs.

##### **14.4.2 Confidentiality of data**

All information regarding the participants will remain confidential to the extent allowed by law. Unique numerical identifiers will be used for data entry. All screening forms and case report forms will be kept in a secured location with access limited to authorized study staff. Unique numerical identifiers will be used for the computer-based data entry and blood samples. Publications will contain only aggregate data; no identifying information will be included.

#### **14.5 ETHICAL CONSIDERATIONS FOR HUMAN PARTICIPANTS**

##### **14.5.1 Risks from blood sampling**

Blood sampling may be inconvenient to the participants, and may cause minor discomfort and bruising. In some aspects of the trial, blood sampling has the potential to directly benefit the participants as any malaria infection or anaemia detected as a result of the sampling will be treated.

The volume of blood collected from each participant will be small; a maximum of 10 mls per child may be collected over the course of the study. Well-trained nurses and laboratory staff employed on the trial will perform blood-sampling tasks. New and sterile disposable needles and lancets will be used for blood taking procedures. Universal precaution measures for blood handling and disposal will be observed when performing the procedures and used needles and other waste will be safely discarded immediately after use.

##### **14.5.2 Safety of study drug in children**

DHP is currently thought to be safe in children. However, adverse events, particularly those associated with the study medication will be recorded and monitored throughout.

##### **14.5.3 Methods to minimise risks**

In order to minimize risks to study subjects, subjects will be encouraged to present to the clinic at any time that they show signs of any illness, fever, or injury. Sterile technique will be used to obtain blood samples and only trained and experienced staff will perform finger prick and venepuncture.

##### **14.5.4 Experience with DP as PMC**

Dihydroartemisinin-piperaquine (DP), the drug combination that will be used in this trial, is one of the artemisinin containing combination therapies (ACTs). ACTs are now the standard for treatment of *P.falciparum* malaria in both adults and children [22]. A systematic review of the efficacy and safety of ACTs for the treatment of malaria in children conducted to inform the 2nd edition of the malaria treatment guidelines by WHO, showed that DP is very effective and provides a long duration of post-treatment

prophylaxis, similar to mefloquine and longer than amodiaquine (AQ-artesunate, or AQ-SP) and artemether-lumefantrine (Coartem®) based antimalarial combinations [23].

Because of its long half-life, piperaquine (PQ) has great potential for use as the ACT of choice for Intermittent Screening and Treatment (IST) and IPT, as was shown in IPTc studies in children [24].

Furthermore a trial with monthly DP used as IPT in Thai adults showed it to be well tolerated, safe, and highly effective [8]. In that trial the most important determinant of protective efficacy was the trough plasma concentration of piperaquine, and this was determined by the dosing frequency. Although an acceptable protective efficacy of 86% was achieved with dosing every 2 months, the drug concentrations required for successful prevention of malaria infections are not maintained in between doses. Compared with participants receiving monthly DP dosing, participants who received dosing every 2 months were 8 times more likely to get malaria (adjusted hazards ratio [AHR], 8.24; 95% CI, 3.25 to 20.9), and participants in the placebo group were 41 times more likely to get malaria within 9 month (AHR, 41.3; 95% CI, 16.6 to 102.8). This suggests that for effective prevention of malaria, DP should be given monthly in order to achieve steady state concentrations above the minimum inhibitory concentrations and sustained prophylactic levels [8].

PQ is currently only available in the fixed dose combination with dihydro-artemisinin (DHA) as DP. The DHA component, eliminated within a few hours, is not expected to provide a significant contribution to the effect of IPTp, yet may provide a degree of protection against the development of PQ resistance in the population. A GMP formulation of DP has recently become available as Eurartesim, manufactured by Sigma-Tau, Italy and approved in October 2011 by the European Medicine Agency (EMA) for treatment of malaria

Piperaquine is well tolerated. Side effects in adults include transient drops in haemoglobin by day 7 (seen with all artemisinins), headache, weakness and fever. The main safety concerns with piperaquine relate to its dose-dependent QTc prolongation. Mild levels of QTc prolongation has been confirmed in clinical trials, but these were mild and similar to many other anti-malarials [25] and there is no indication from clinical data signalling that it is associated with clinically significant arrhythmias [26] This is consistent with recently in-vitro models which confirmed that despite mild QTc prolongation the potential cardiac proarrhythmic risk with piperaquine is low and similar to that observed with lumefantrine (the long-acting component in Coartem), and lower than for chloroquine. This study concluded that DP does not appear to induce potential torsadogenic effects in vitro (which could result in life threatening abnormality of heart rhythm).

#### **14.5.5 Anticipated benefits to study participants**

By taking part in this trial, participants will receive PMC-DHP in whom we expect to treat infections that may otherwise remain undetected. Participants who do not attend scheduled appointment will receive reminders and active follow-up. Participants experiencing illness between visits will be seen and treated free of charge as part of the study.

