|                                            |                         |                               |                       |                                                                                                                                                                           | X        | X        | X                    |          | X        | X                       | X         |           |                       |
| Patient costs                              |                         |                               | X                     |                                                                                                                                                                           |          |          |                      |          |          |                         |           |           | X                     |

Visit #1: Enrolment and randomisation at discharge

Visit #2 #3#4: Home visits at 6, 10 and 14 weeks after enrolment to assess uptake of the 1st, 2nd and 3rd treatment course of the PMC study drugs respectively.

Visit #5: at 3.5 months after enrolment. This is the close out assessment.

---

- a. Children can be pre-study screened any time between hospital admission and enrolment. The figure of -4 days is provided for illustration purposes only.
- b. Visit window= number of days an actual subject visit may fall outside of the planned protocol schedule visit to still meet protocol requirements. DP should be given at least 4 weeks apart.
- c. MS, malaria smear. This will be collected for research purposes only, and read days to weeks later. Malaria smears will not be used for point of care. If participants are symptomatic (e.g. fever) an RDT will be taken for point of care.
- d. VP=vena puncture. FP=finger prick, DP=dihydroartemisinin-piperaquine, , Hb=haemoglobin, MS=malaria smear, Pf=Plasmodium falciparum

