### **7.2 Specific objectives**

1. To compare PMC uptake (adherence) levels between community- versus health facility-based strategies
2. To determine whether SMS or Health Surveillance Assistant (HSA) reminder has additional benefit on PMC uptake (adherence) levels
3. To determine the safety of PMC delivery in the community versus in the health facility
4. To determine and compare the cost to the health service of delivering PMC using each individual delivery strategy
5. To determine and compare the cost to the patients and guardians of receiving PMC using individual delivery strategies
6. To determine the feasibility and acceptability of delivery of PMC in a typical Malawi health system setting

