## 8 DESIGN AND METHODOLOGY

### 8.1 Trial Design

This is a single-centre, matched, cluster randomized, 5-arm, factorial design trial comparing the uptake of PMC-DHP delivered through health facility or community-based approaches with or without SMS/HSA reminders. All children will receive DHP and hence there are no placebo arms in this trial. However, children shall be randomized to receive PMC as follows:

- a. *Community-based*: Mother given **all** PMC drugs at discharge without an SMS reminder
- b. *Community-based*: Mother given **all** PMC drugs at discharge with an SMS reminder
- c. *Community-based*: Mother given **all** PMC drugs at discharge with HSA reminder
- d. *Facility-based*: Mother asked to return to outpatient departments (OPD) for each **monthly** PMC without an SMS reminder
- e. *Facility-based*: Mother asked to return to outpatient departments (OPD) for each **monthly** PMC with an SMS reminder

Where;

**Arm 1: Mother given at discharge without SMS reminder:** At discharge, the OPD staff will give the mother or guardian all drugs for PMC-1, PMC-2 and PMC-3 and instruct mother/guardian when to give these drugs.

**Arm 2: Mother given at discharge + SMS reminder:** At discharge, the OPD staff will give the mother or guardian all drugs for PMC-1, PMC-2 and PMC-3 and instruct mother/guardian when to give these drugs. Additionally they will be reminded via SMS to give the drugs to the child a date before each treatment course is due.

**Arm 3: Mother given at discharge + HSA reminder:** At discharge, the OPD staff will give the mother or guardian all drugs for PMC-1, PMC-2 and PMC-3 and instruct mother/guardian when to give these drugs. Additionally HSA or Village Health Volunteers (VHV) which are part of existing networks of community based volunteers taking part in village health committees will be reminded via SMS to go and remind the mother to give the drugs to the child a date before each treatment course is due.

**Arm 4: Mother given monthly at OPD without SMS reminder:** At discharge, the mother will be requested to return to the OPD to collect drugs for PMC-1, PMC-2 and PMC-3.

**Arm 5: Mother given monthly at OPD + SMS reminder:** At discharge, the mother will be requested to return to the OPD to collect drugs for PMC-1, PMC-2 and PMC-3. Additionally they will be reminded via SMS to come to the clinic to collect drugs a date before each treatment course is due.

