## 8.9 OUTCOMES

### 8.9.1 Primary Outcome

The primary outcome is the 100% of PMC drugs uptake (defined as administration of **all** 3-day treatment courses, given 2, 6 and 10 weeks after discharge) assessed by unannounced spot checks.

The PMC uptake will be assessed through a study questionnaire administered at unannounced spot checks to determine if and when children and their mothers/guardians attend the scheduled dosing of the drug. The spot checks will be conducted at day 4 or 5

of each DHP treatment course. The effectiveness of the delivery mechanism will be determined by the following measures:

1. **Pill count:** Research Assistants will perform a pill count of the drugs available at the day of the visit. This will be used to assess whether participants took the whole course of DHP or not.
2. **Interview:** A face-to-face interview with the mothers/guardians of children participating in the study will be done to collect information on missed doses and possible reasons for any missed doses.

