#### 8.12.4 1st, 2nd and 3rd PMC treatment schedules

The 1st, 2nd and 3rd PMC treatment will be given 2, 6 and 10 weeks following enrolment. These treatments will be given at home for those randomised to Arm 1, 2 or 3 and at OPD for those randomised to Arm 3 and 4 (Day 1 dose only, Day 2 and 3 will be at home). PMC uptake will be assessed by unannounced visits on day 4 or 5 after each treatment course by a research assistant. If children are found to be ill during these home-visits they will be referred to the study clinic for further evaluations as part of the unscheduled visits as described below.

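### Section 14.5.5 promises reminders after any missed appointment without excepting the no-reminder OPD arm, and two of the three stated home-visit timings fall when courses are due

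*Protocol*

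**What the plan says.** Section 14.5.5, on anticipated benefits, states "Participants who do not attend scheduled appointment will receive reminders and active follow-up". It does not define the appointment and does not limit the statement to any arm or visit.

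Section 8.1 defines two arms without reminders: "Arm 1: Mother given at discharge without SMS reminder" and "Arm 4: Mother given monthly at OPD without SMS reminder". Arm 4 mothers are asked to return to the OPD for each of the three courses. Arm 1 mothers take all the drugs home at discharge. (Section 8.1.1 swaps the labels of Arms 4 and 5; I follow 8.1 and Figure 1.)

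The reminder is a randomised factor. Specific objective 2 in section 7.2 reads "To determine whether SMS or Health Surveillance Assistant (HSA) reminder has additional benefit on PMC uptake (adherence) levels", and section 8.3 names the main effects of delivery mode and reminder use as those of primary interest.

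On course dates, section 8.12.4 says "PMC treatment will be given 2, 6 and 10 weeks following enrolment". The visits that assess uptake are timed in three ways:
- Table 2 notes (section 4.2): "Home visits at 6, 10 and 14 weeks after enrolment to assess uptake of the" first, second and third course respectively.
- Section 8.12.1: home visits to a subset at 2, 6 and 10 weeks.
- Section 8.9.1: "The spot checks will be conducted at day 4 or 5" of each course, unannounced. Section 8.12.4 agrees in substance.

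Section 8.7.6.2, on retention, describes telephone calls and home tracing only for children who miss the Study End visit.

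**The concern.** A reminder comparison needs the comparator families to go unreminded by the study. Two parts of the protocol work against that.

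First, an Arm 4 drug collection is a scheduled visit on any ordinary reading. Staff who follow 14.5.5 literally would contact an Arm 4 mother who misses one, and so deliver something close to the intervention under test.

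Second, a research assistant who arrives to ask about study drugs in the week a course is due is a cue to give that course. This applies in all arms, including Arm 1, where 14.5.5 has no drug-collection appointment to act on.

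Contact triggered by non-attendance falls most on the arm with most non-attenders, so the likely bias in the reminder effect is towards no difference. The OPD arms have collection appointments and the discharge arms do not. The first route could therefore also raise OPD uptake against home delivery. Neither effect can be removed in the analysis once families have been contacted.

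**Working it through.** **Timing, set against the due weeks (2, 6 and 10)**

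| Source | Visits | Visits in a due week |
|---|---|---|
| Table 2 notes | weeks 6, 10, 14 | weeks 6 and 10 (courses 2 and 3) |
| Section 8.12.1 (subset) | weeks 2, 6, 10 | all three |
| Sections 8.9.1, 8.12.4 | day 4 or 5, unannounced | none; each comes after the three dosing days |

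**Reproducing the planned power**

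Inputs from section 8.3: 75 children per arm, 10% loss, mean cluster size 3, SD 0.58, ICC 0.1, uptake 50% versus 75%, α = 0.05. Sidedness is not stated; I assume two-sided.

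- CV² = 0.58²/3² = 0.037
- Design effect = 1 + [(1 + 0.037) × 3 − 1] × 0.1 = 1.211
- Effective n per arm = 75 × 0.9 / 1.211 = 55.7
- Power = Φ( d / √[(p₁(1−p₁) + p₂(1−p₂))/n] − 1.96 )
- Planned case: 0.25 / √(0.4375/55.7) = 2.82, so power = Φ(0.86) = 80.6%. With a pooled variance it is 78.6%.

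This agrees with the 80% in section 8.3. The 90% in the section 4.2 summary does not reproduce and is not used.

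**Illustration of dilution**

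The protocol gives no contamination rate. I assume that a share c of children who would not complete all courses is converted by study contact.

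- No-reminder arm: 0.50 + 0.50c.
- Reminder arm, if equally affected: 0.75 + 0.25c. The difference is then 0.25(1 − c).
- Pooled reminder effect (Arms 1 and 4 against Arms 2 and 5), with only Arm 4 affected: the no-reminder side is the mean of 0.50 and 0.50 + 0.50c, with effective n = 2 × 55.7 = 111.4 per side.

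| c | One arm against another, both affected | One arm against another, only no-reminder arm affected | Pooled effect, only Arm 4 affected |
|---|---|---|---|
| 10% | 55% vs 77.5%: 73% | 55% vs 75%: 62% | 52.5% vs 75%: 95% |
| 20% | 60% vs 80%: 66% | 60% vs 75%: 40% | 55% vs 75%: 89% |
| 25% | 62.5% vs 81.25%: 61% | 62.5% vs 75%: 30% | 56.25% vs 75%: 85% |

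The last figure in each cell is power. With no contamination, the pooled effect has about 98% (0.25 / √(0.4375/111.4) = 3.99; Φ(2.03)).

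**Delivery comparison**

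The plan puts Arms 1 and 4 both at 50%. If only Arm 4 is lifted, the spurious OPD advantage is 0.50c: 5, 10 or 12.5 points for the same three shares.

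**The case against.** The strongest reply is that 14.5.5 is a general sentence about benefits, not an operating procedure. The section that does give procedures, 8.7.6.2, traces families only for the Study End visit, and Arm 4 is specified without a reminder. No operational section prescribes contact after a missed drug collection. This stands to the extent that the protocol does not show that the no-reminder arms will be reminded. A reader might infer that from 14.5.5, but the documents support only an unrestricted promise that conflicts with the arm definition. The sentence still needs a limit, because nothing in the text supplies one.

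A reader might also infer that 14.5.5 contaminates the named control. It does not do so through drug collections, because Arm 1 has none to miss. Only the home-visit timing can reach Arm 1.

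On timing, the Table 2 note sits badly with its own grid, which places the visits at weeks 2, 6 and 10. Section 8.12.1 may be loose shorthand for the round of spot checks, and both full descriptions of uptake assessment use day 4 or 5. That is a good reason to settle on the spot check, but the other two timings remain in the text.

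Late prompting also has limited power to rescue the primary outcome. All three courses must be taken, and a child already scored as missing one cannot recover. A prompt helps only if the course is finished before its check. This caps the first route without closing it.

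Finally, every family already has the dates in the health passport and on a card (section 8.7.6.1). That is common background across arms. Contact triggered by non-attendance is not.

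**Conclusion.** The concern holds as a conflict in the text that bears on the randomised reminder contrast. The promise in 14.5.5 is open to Arm 4 as written. Two of the three home-visit timings fall when courses are due and could prompt dosing in every arm. The expected direction is dilution of the reminder effect, with possible inflation of OPD uptake from the first route.

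The size is not known. The power figures rest on assumed conversion shares of 10% to 25%, a two-sided test and the section 8.3 inputs. The tempting stronger reading is that the reminder comparison drops to 30%–40% power. That needs 20% to 25% conversion confined to the no-reminder arm of a single pairwise contrast. It does not describe the pooled reminder effect, which keeps about 85% or more with only Arm 4 affected. Nor does it fit a mechanism that also reaches the reminder arms, where power is 61%–73%.

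**What to change.** 1. In 14.5.5, state that study reminders and active follow-up apply to the Study End visit, as in 8.7.6.2. Add that a missed drug collection triggers no study reminder before uptake of that course has been assessed.
2. Reconcile the Table 2 notes and section 8.12.1 to the unannounced day 4 or 5 spot check of 8.9.1 and 8.12.4.
3. Instruct visitors in all arms not to prompt the next course.

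The cost is protocol wording and a line in visitor training. Care for illness and passive surveillance are unchanged. The small downside is that families who miss a collection receive less study contact. The consent pages are not in the copy reviewed, so I make no claim about their wording.

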#### **14.5.6 Benefit to the community**

This project is designed to generate the information required to assess whether PMC should be recommended as a cost-effective strategy for the post-discharge management

of children with severe anaemia in malaria endemic areas. It is anticipated the trial results will increase the effectiveness of the management of severely ill children and reduce the health care costs associated with high readmission rates post-discharge, thereby also reducing associated costs to poor households. Women, who are the primary care takers and also key actors for household's economic development, will be relieved and consequently improved welfare for households is expected. In the longer term, the ultimate beneficiaries of this research will be the children in sub-Saharan Africa, whose quality of life, health, welfare and creative output will be enhanced.

#### **14.5.7 Reimbursement of costs**

The study will provide payment for all study drugs, study procedures, study-related visits and reasonable medical expenses that are incurred as a result of the study including expenses for transport for any study related visits.

### **14.6 Ancillary and post-trial care**

#### **14.6.1 Health care during the trial**

All care directly related to the proper and safe conduct of the trial, and the treatment of immediate adverse events related to trial procedures will be provided free of charge by the local hospitals. The provision of ancillary care beyond that immediately required for conduct of the trial will not be covered by the trial. The use of a health passport or national equivalent will aid the identification of study children.

#### **14.6.2 Trial insurance**

The sponsor will take out trial insurance such that participants enrolled into the study are covered by indemnity for negligent harm and non-negligent harm associated with the protocol. This will include cover for additional health care, compensation or damages whether awarded voluntarily by the Sponsor, or by claims pursued through the courts. The liability of the manufacturer of the trial drug DP is limited to those claims arising from faulty manufacturing of the commercial product and not to any aspects of the conduct of the study.

#### **14.6.3 Post-trial care**

The study budget is not in a position to fund post-study care or implementation of PMC as policy. However, the investigators work in close collaboration with local and international policy makers (e.g. WHO) and funders (e.g. President Malaria Initiative) to ensure that policy makers and funders are informed early of germane research finding and can plan for the potential implementation of PMC as policy in the study areas and other relevant areas in Malawi and the region.

